### 2.10. Sampling Procedure

A multi-stage sampling technique will be employed to select study participants. A total of 20 clusters of sub-counties will be selected and included in the study, based on the power calculation. Sub-counties with largest numbers of pregnant mothers registered by the VHTs will be included to ensure that the estimated study sample size is met. This will be used to increase the level of efficiency of sampling and each cluster will be considered as a sampling unit. At the beginning of the study, the team will consult the ttC registers from the VHTs in Hoima and the VHT registers from Masindi to assess the pregnancy registration per sub-county. For each sub-county, six villages will be randomly selected, with each village providing 10 households.

At the household, selection of pregnant mothers to be included in the study will be done systematically. In this probability sampling, participants will be selected from a larger population of pregnant mothers according to a random starting point and a fixed periodic interval. This periodic interval will be determined beforehand as two, which means that assuming the starting point is one as the first serial number on the VHT register, every pregnant mother with an even serial number will be selected to participate in the study, that is, 2, 4, 6, 8, etc. The sampling procedure is presented in Figure 3.

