### 2.2. Study Site

The study will take place in the districts of Hoima (intervention district) and Masindi (control district) in the Bunyoro sub-region in western Uganda. ttC will be implemented in the Hoima district, because this district has one of the highest maternal mortality rates in Uganda [14]. Masindi has been selected as the control district because it has a similar profile of maternal, newborn and child health determinants compared to Hoima. Some examples of similarities in key indicators for Hoima [15] and Masindi [16] are the number of females aged 18 years and above who are illiterate (38.4%, and 39.5%, respectively)**,** children aged 0–17 who lost both parents (0.7% and 0.2%), females aged 12–17 who have ever given birth (11.8% and 10.5%), and households located 5 km or more from the nearest health facility (39.5% and 29.5%).

Both Hoima and Masindi have functional VHTs who have received basic training on the roles and responsibilities in the delivery and reporting of community health. They have also received the necessary materials to assist them in their work and the two districts had VHT capacity assessed for their level of functionality before the training. All VHTs [17] in Uganda must undergo a five-day training course, be equipped with a participant’s manual, a household register, cards for counselling purposes and a monthly reporting book before they are fully qualified to provide community health services. Partners who wish to provide additional capacity-building to the VHTs first make sure that the VHTs are trained in the general strategy. However, for the intervention district, additional training has been done to facilitate the implementation of ttC to improve MNCH indicators and deliverables.

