### 2.6. Intervention

The ttC intervention will be rolled out as a behavioral change communication model for the first 1000 days. For ttC to be implemented, a five-day central hands-on training is conducted for the VHTs (intermediaries), using a two-way counselling approach (participatory approach). The training will be conducted by VHT supervisors who are trained as trainers in the course for 10 days. These VHTs are then expected to translate the acquired knowledge to the expectant mothers and mothers with neonates as they deliver the ttC package during their home visits.

In the WHO’s review of global CHW training resources [18], ttC emerged as one of the most comprehensive curricula available in terms of its range of technical content, and spectrum across the continuum of care. ttC takes a life-cycle approach, focusing on supporting for the period from pregnancy up to two years of age. We believe that providing care on this continuum offers the best opportunity to ensure that children are on a path to life-long health. Taking a more family-centered approach, in ttC VHTs learn practical skills for addressing barriers to MNH, promoting involvement of fathers, and enabling CHWs to identify barriers to health [19].

VHTs are taught how to handle the household heads, any other influential individuals and the expectant mothers or mothers with neonates. During the training, the VHTs are equipped with a participant’s manual, a ttC-specific household register to note down all pregnant mothers and kick-start the timely follow-up process as scheduled in the ttC guideline [20].

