### 2.11. Study Instruments

The study collects data from existing registries as well as through questionnaires:The Ugandan VHT household register (VHTR): This will be the entry basis into the community for both study sites. All mothers to be included in the study must have been registered by the VHT at the household level in this household register.The ttC register (ttCR): This will provide the data required for the intervention implementation analysis (process evaluation). It will also be the entry point for mothers to be included in the study and the VHTs are responsible for documentation using this register. The tool captures day-to-day visit activities between the household and the VHT.Study Questionnaire (SQ): This has been developed specifically to collect data that will be used for outcome results at the end of the intervention. An expert staff member in ttC has provided guidance that led to the revision of the tool in line with the sub-objectives. Furthermore, two researchers were asked to critically review the tool in line with the standard objectives. Their comments have been incorporated into the tool. More pre-testing of the tool will be done at the field level during the training of the enumerators.

These instruments and the variables assessed are described in more detail below.

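### Sub-counties are ranked by registered pregnancies from an intervention register in Hoima and a routine register in Masindi, so cluster selection can differ between the arms

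*Protocol article*

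**What the plan says.** Section 2.10 (Sampling Procedure) takes 20 sub-counties as clusters. They are not drawn at random: "Sub-counties with largest numbers of pregnant mothers registered by the VHTs will be included", the stated reason being to reach the sample size. To obtain the counts, the team will "consult the ttC registers from the VHTs in Hoima and the VHT registers from Masindi". Chance enters only below this level, where six villages per sub-county are drawn at random, each supplying 10 households. Women are then taken from the VHT register at an interval of two.

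Three other places bear on the choice of register:

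- Section 2.6 (Intervention): at ttC training the VHTs are given "a ttC-specific household register to note down all pregnant mothers", which also starts the follow-up visits.
- Section 2.2 (Study Site): "for the intervention district, additional training has been done to facilitate the implementation of ttC". No such training is described for Masindi.
- Section 2.11 (Study Instruments) says of the Ugandan VHT household register: "This will be the entry basis into the community for both study sites". Every included mother must appear in it. The same section assigns the ttC register to the process evaluation, while also calling it an entry point.

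**The concern.** A count of registered pregnancies is the number of pregnancies multiplied by the share that the VHTs find and write down. Section 3.2 accepts that this share varies: women tend to hide pregnancies, and VHTs who cannot read may both support households less well and record less. One VHT characteristic therefore affects the variable used to pick clusters and the care on which the outcomes depend.

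In Masindi the count comes from the routine register. In Hoima it comes from a tool that exists only because of ttC, and Table 1 links registration as a ttC candidate to the first ttC visit. Ranking Hoima on that tool partly ranks its sub-counties on how well ttC has started there. No reason is given for using two sources when a common one exists.

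Comparability is at stake. With one district per arm and no randomisation, the comparison relies on the two samples having been chosen alike. The models in section 3 adjust for confounders and for clustering within villages, but they cannot bring back sub-counties that were never eligible. Section 3.2 does not list this among the limitations.

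**Working it through.** **The plan's own figures.** Section 2.8: 1107 × 1.10 = 1217.7, rounded to 1218, which reproduces. Then 1218 / 60 = 20.3, stated as 20 clusters, the same number per arm, so 10 per district. Section 2.10: 20 × 6 × 10 = 1200, close to 1218.

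**The two arms side by side.**

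| Step | Hoima | Masindi |
|---|---|---|
| Rule for sub-counties | largest registered count | largest registered count |
| Source of the count | ttC register | VHT register |
| Source issued as part of ttC | yes (2.6) | no |
| Villages | random, six | random, six |
| Women must be in the VHT household register | yes (2.11) | yes (2.11) |

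The arms differ in the source of the count and nowhere else in this table.

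**How strongly the rule selects on VHT performance.** The article does not give the number of sub-counties per district or the spread of registration completeness, so both are assumed here. Model: registered count = true pregnancies × completeness. Log true size has SD 0.3, log completeness has SD 0.1 to 0.3, the two are independent, and the 10 largest of M sub-counties are taken (20,000 simulated districts per setting). The entries are the mean completeness of the selected sub-counties above the district average, in SDs of log completeness.

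| M | SD 0.1 | SD 0.2 | SD 0.3 |
|---|---|---|---|
| 11 | 0.05 | 0.09 | 0.11 |
| 13 | 0.12 | 0.20 | 0.26 |
| 16 | 0.18 | 0.32 | 0.41 |
| 20 | 0.24 | 0.43 | 0.55 |

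With M = 10 the shift is zero, because every sub-county is taken.

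**What this means for the contrast.** If M and the spread are the same in both districts, the shift is the same in both and the gap in completeness between arms is zero. A gap needs a difference, which two registers can create. For example, with M = 13 in both and a spread of 0.3 in Hoima against 0.1 in Masindi:

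- Hoima: 0.26 × 0.3 = 0.078, and exp(0.078) = 1.08, so completeness is about 8% above the district average.
- Masindi: 0.12 × 0.1 = 0.012, and exp(0.012) = 1.01, about 1% above.

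With the two spreads exchanged, the gap has the same size and the opposite sign. The article gives nothing that links completeness to the outcomes, so none of this converts into percentage points.

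**How many registered women a sub-county needs.** Ten women per village at an interval of two requires 10 × 2 = 20 registered women per village. Six villages require 6 × 20 = 120, before the replacement of drop-outs described in section 2.9. The 60 women finally sampled per sub-county are therefore not a sufficient threshold.

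**The case against.** The strongest reply is that one rule governs all 20 clusters. Masindi also contributes its highest-registering sub-counties, so active VHTs are favoured in both arms. Selection common to both arms restricts the population to which the result applies and does not by itself bias the contrast. This stands. A reader might infer that Hoima is enriched by a criterion that Masindi lacks. Section 2.10 contradicts that: only the register differs.

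Secondly, a large count need not mean good counselling. It also reflects population size and fertility, and recording a woman is not the same as counselling her. Section 2.10 has the registers consulted at the start of the study, and Table 3 begins ttC implementation in January 2020, after the baseline columns. This stands in part. An early count may say little about the quality of delivery. But if the ttC register is issued at ttC training, as section 2.6 describes, its count cannot predate that training.

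Thirdly, the plan gives a feasibility reason for taking the largest sub-counties, and the need for about 120 registered women shows that the reason has substance. This stands for the largest-count rule. It does not explain the use of different registers.

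Finally, the requirement that every mother be in the common household register, with random villages, limits the asymmetry to the sub-county stage. That is right, and the point is confined to that stage.

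**Conclusion.** The point holds as an arm-dependent selection step. Sub-counties in the two districts are ranked on different registers, one of them part of the intervention, although the article names a register used at both sites. Since registration depends partly on VHT performance, the chosen sub-counties may differ between arms in a way that favours better early ttC uptake in Hoima.

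The documents do not support more than that. A reader might infer that the comparison is biased towards ttC by a definite share of the planned 10-point effect. Neither the direction nor the size is shown. On the assumed inputs above, selected sub-counties lie 0.05 to 0.55 SD above their district's average in registration completeness. The shift is zero if a district has only 10 sub-counties, and only the difference between districts would affect the contrast. The largest-count rule itself is mainly a limit on generalisability, which matters because section 3.1 intends the Ministry of Health to replicate the findings elsewhere.

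The change is worth making because it is cheap and because later analysis cannot undo the selection.

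**What to change.** 1. In section 2.10, take the counts for both districts from the same source at the same date: the VHT household register, before ttC roll-out where such counts can be recovered. The 2019 health management information system reports cited in section 2.8 are an alternative if they exist by sub-county; the article mentions them only for the districts.
2. If feasible, select 10 sub-counties per district at random or with probability proportional to size, among those with enough registered women for the stated sampling: about 120 in the six villages, plus an allowance for replacements.
3. If that is not feasible, keep the largest-count rule on the common source and state in section 3.2 that the results apply to high-registering sub-counties.
4. In either case, report how many sub-counties each district has and how many were left out. This shows how much selection took place. If the sub-counties have already been chosen, also report how the choice compares with a ranking on the common register.

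The first item matters most; the second is a trade-off against feasibility. The cost is some work to extract the common register counts and, under random or size-proportional selection, slightly slower recruitment in some sub-counties.

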### 2.8. Sample Size

The sample size is calculated using the formula for comparing differences in rates and proportions between two groups and determining the number of subjects per group^n^, using an individual binary for a two-sided significant level α and power 1-β [27]. With an anticipated effect size of 10% [δBinary = (^μ^T − ^μ^C)], α = 0.05 (two-sided), β = 0.2,^ z^1^−α^/2 = desired significance level at 95% (0.05). ^Ζ^1 − β = desired power at 80% (0.842), type of test = two-sided, and absolute risk reduction = 10%.

Since the study focuses on uptake of pregnancy services and essential newborn care, the key participants are pregnant mothers. We, therefore, estimate the pregnancy rate from each area using the 2020 population estimates per district, then turning the pregnancy rate into a percentage proportion. To estimate pregnancy rate, the focus will be on the recommended women of reproductive age within the population. Using the health care planning estimation, it is estimated that 24% of the population are women of reproductive age [28]. An estimation of number of births, abortions and foetal losses was acquired from the actual total 2019 health management and information systems [29] reports for both districts. This provided a 1107-sample size in the two districts. This will be increased by 10% to 1218 participants to cater for a non-response. Therefore, the treatment and control groups will each have 609 mothers at the end of the study.

To determine number of clusters needed (n_cluster) [27,30]: n _cluster = total number of participants in the two groups (/fixed cluster size) which is (^n^Cluster_Binary 2)/m = 1218/60, giving us 20 clusters. In order to have the same number of clusters per arm, the number of clusters will be increased to the nearest upper even number, which is 20 in this study. This means that the sample size contains 1218 pregnant mothers in 20 clusters which is the sub-county by the administrative units of Uganda [31].

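### The start, interval and take per village of the systematic sample do not agree, and the even-serial rule, if it is the one applied, is neither random nor hidden from the VHTs

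*Protocol article*

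**What the plan says.** All the sampling statements are in section 2.10 (Sampling Procedure) of the protocol article.

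- Within each selected sub-county, "six villages will be randomly selected, with each village providing 10 households".
- Selection is called probability sampling, made "according to a random starting point and a fixed periodic interval".
- On the interval: "This periodic interval will be determined beforehand as two".
- On the start, the rule is worked out "assuming the starting point is one as the first serial number on the VHT register".
- The result is that "every pregnant mother with an even serial number will be selected to participate in the study", with the series begun as 2, 4, 6, 8 and left open. No last serial is given.

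Section 2.8 (Sample Size) uses a cluster size of 60: "1218/60, giving us 20 clusters".

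Other sections bear on who could know the rule. VHTs make the register entries through which women come into the study (2.11), deliver ttC on home visits (2.6) and facilitate written consent (2.3). Section 2.9 has women enrolled as they become pregnant, so serial numbers are still being issued while the study runs.

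**The concern.** Three elements define a systematic sample: where it starts, the interval, and how many units it must yield. Here they do not fit together.

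A random start is promised, but the only start named is serial one. That start with the stated interval does not ordinarily give the stated serials. The interval is then fixed at two for every village, whatever the length of its register, while the yield is fixed at 10.

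Two things are at stake. The first is whether the women evaluated represent the registered women: under a standing even-serial rule, odd-numbered women are never eligible for selection. The second is foreseeability. A VHT who knows that even serials are evaluated knows, when writing an entry, whether that woman will count. Order of entry, or effort on later visits, could follow from that knowledge. In Hoima, extra effort for even-numbered women would make ttC look better than it is for registered women in general. Treatment is set by district, so this does not concern concealment of allocation.

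**Working it through.** **Inputs.** From section 2.10: interval k = 2, assumed start s = 1, stated serials 2, 4, 6, 8, take of 10 households per village, 6 villages per sub-county. From section 2.8: cluster size 60, 20 clusters, total 1218. Assumptions: one serial list of pregnant women per village and one woman per household. Register length L is not given, so a range is used.

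**1. The plan's own totals.** 6 × 10 = 60 per sub-county, which matches the cluster size in 2.8. 1218 / 60 = 20.3, taken as 20. 20 × 60 = 1200, which is 18 below 1218. The take of 10 is therefore what supplies the planned cluster size.

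**2. The serials.** The usual rule is serial(j) = s + (j − 1) × k.

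- s = 1, k = 2: 1, 3, 5, 7, …, 19 for the first ten.
- s = 2, k = 2: 2, 4, 6, 8, …, 20 for the first ten.

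The stated series does not follow from the stated start. It can be reached by counting names from one and taking every second name, but then the start is fixed rather than drawn.

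**3. Selection probabilities at interval two.**

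- Start drawn at random from {1, 2}: every woman has probability 1/2.
- Even serials always taken: even-numbered women have probability 1 and odd-numbered women 0.

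**4. Interval against take.** Taking every even serial selects L/2 women. The interval that spreads 10 selections over the whole list is L/10.

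| Register length L (assumed) | Women on even serials | Interval that would give 10 |
|---|---|---|
| 10 | 5 | 1.0 |
| 16 | 8 | 1.6 |
| 20 | 10 | 2.0 |
| 30 | 15 | 3.0 |
| 40 | 20 | 4.0 |
| 60 | 30 | 6.0 |

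Interval two and a take of 10 agree only at L of about 20. Below that the village falls short: if all six villages in a sub-county had 16 women, the yield would be 6 × 8 = 48 rather than 60. Above it, the text does not say which even-numbered women are left out.

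**5. Effect of non-participation.** If a share q of selected women is eligible and consents, 10 enrolments need about 10/q selections, and the tenth enrolled woman is expected near serial 20/q: 22 at q = 0.9, 25 at 0.8, 29 at 0.7 (q assumed). This shifts the length at which interval and take agree; it does not make them agree in general.

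**The case against.** The strongest reply is that the operative rule is the general one. Only the interval is said to be settled beforehand. The start of one is introduced as an assumption and can be read as an illustration. On that reading every woman has probability one half before the draw and the sampling is sound. Figure 3, which presents the procedure, is not shown and may settle the start. The reply stands far enough that the zero-probability conclusion must be conditional. It does not remove the inconsistency: the illustration does not follow from its own premises, the text gives no other working rule, and a random start would not reconcile interval two with a take of 10.

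The reply on foreseeability is that nothing says VHTs are told the rule. Section 2.10 has the study team consult the registers, and section 2.6 has VHTs convened monthly to keep them to their visits. That is fair, and the point is accordingly a risk. But a constant parity rule is easy to learn, and nothing in the text keeps it from those who write the entries.

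A reader might infer three stronger things that the documents do not support.

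- *Selection stops at serial 20.* No stopping point is stated, and the series is left open. Twenty is only 10 × 2. It needs one register per village and every selected woman enrolled, whereas section 2.9 provides for eligibility screening and replacement of dropouts. Section 2.9 also lets the register grow, so a short register at one date does not prove that 10 can never be reached.
- *Women with early ANC are over-represented.* Under rolling enrolment a low serial means entry earlier in calendar time. It does not mean registration earlier in pregnancy, and no link to ANC timing is shown.
- *VHTs have manipulated, or will manipulate, the registers.* Nothing in the article documents this.

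**Conclusion.** The point holds in this form. The start, the interval and the take per village in section 2.10 are mutually inconsistent and need to be reconciled before sampling. The stated serials do not follow from the stated start under the usual rule, and interval two matches 10 per village only for registers of about 20 women.

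If the even-serial rule is the one applied, three consequences follow: the start is not random, half of the registered women have no chance of selection, and VHTs could foresee who will be evaluated. The size of any resulting bias cannot be calculated, because register lengths and VHT knowledge of the rule are not given. The mismatch figures rest on assumed register lengths, one list per village and one woman per household.

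This is a correctable weakness in how women enter the sample. It does not affect how treatment is assigned.

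**What to change.** 1. Delete the sentence that fixes selection on even serials.
2. Have the study statistician draw a random start separately for each village, between 1 and that village's interval. Where the interval is two, this is a random choice of odd or even.
3. Have the study team, not the VHTs, apply it to the register, and do not disclose the start to the VHTs beforehand.
4. Reconcile the interval with the take of 10. Where the list is closed at sampling, use register length divided by 10. Under the rolling enrolment of section 2.9, where no closed list exists, use the expected number of registrations over the enrolment period divided by 10.
5. State what happens when a village yields fewer or more than 10.

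Keeping interval two and randomising only odd or even would repair the start but leave the conflict with the take of 10, so step 4 is needed as well. The cost is a few lines of text, a forecast of registrations per village and a random-number list. The small downside is that the study team must draw and hold that list.
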